### 11.5.2.3 OTHER EFFICACY ANALYSES

Exploratory endpoints include additional cognitive and functional status assessments:

These endpoints will be analysed using descriptive statistics of the total scores presented by treatment in each study arm and overall, in both tabular and graphical form. In case of the latter, boxplots will be used for analysis of exploratory functional assessments.

- Barthel Index (see [Section 9.1.4.1](#)) - change from baseline Day 7 (Visit 3) and Day 90 (Visit 5) will be assessed using ANCOVA with baseline Barthel Index score and treatment as independent variables. LS mean difference between placebo and active drug with 95% confidence interval will be provided. If either the equal variance or the normality assumption appears to be grossly violated, other methods including an ANCOVA on ranks model or an appropriate transformation of endpoint might be considered.
- MoCA (see [Section 9.1.4.2](#)) - change from baseline (Day 7) to Day 90 will be analysed in the same way as Barthel Index.
- HADS (see [Section 9.1.4.3](#)) assessment of mental condition collected on Day 7 and Day 90 will be analysed in the same way as Barthel Index.
- IQCODE assessment on Day 7 (see [Section 9.1.4.4](#))
- Brain natriuretic peptide (see [Section 9.1.5](#)) change between baseline (Screening visit) and Day 7 will be analysed in the same way as Barthel Index.

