### 3.3 EXPLORATORY OBJECTIVES

| Objective                                                                                                                                                                                                                                     | Outcome measure / Endpoint                                                                 |
|-----------------------------------------------------------------------------------------------------------------------------------------------------------------------------------------------------------------------------------------------|--------------------------------------------------------------------------------------------|
| To assess BNP or NT-proBNP plasma levels after the investigational therapy in patients with acute ischaemic stroke on the non-vitamin K antagonist oral anticoagulants after administration of a specific reversal agent compared to placebo. | Change in BNP or NT-proBNP plasma concentration at Day 7 compared to pre-treatment levels. |
| To assess functional independence after the investigational therapy in patients with acute ischemic stroke on the non-vitamin K antagonist oral anticoagulants compared to placebo using Barthel Index scale.                                 | Change in Barthel Index score measured at Day 90 compared to Day 7.                        |
| To assess cognitive function after the investigational therapy in patients with acute ischemic stroke on the non-vitamin K antagonist oral anticoagulants compared to placebo using MoCA scale.                                               | Change on MoCA scale measured at Day 90 compared to Day 7.                                 |
| To assess pre-stroke cognitive function after the investigational therapy in patients with acute ischemic stroke on the non-vitamin K antagonist oral anticoagulant compared to placebo using IQCODE scale.                                   | Assessment of pre-stroke cognitive impairment measured by IQCODE scale at Day 7.           |

|                                                                                                                                                                                                                               |                                                            |

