|-------------------------------------------------------------------------------------------------------------------------------------------------------------------------------------------------------------------------------|------------------------------------------------------------|
| To assess “mental” condition (i.e. depression and anxiety) after the investigational therapy in patients with acute ischemic stroke on the non-vitamin K antagonist oral anticoagulants compared to placebo using HADS scale. | Change on HADS scale measured at Day 90 compared to Day 7. |
| To assess duration of the hospitalisation after the investigational therapy in patients with acute ischemic stroke on the non-vitamin K antagonist oral anticoagulants compared to placebo.                                   | Number of days from the hospital admission to discharge.   |

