#### 9.1.4 ADDITIONAL FUNCTIONAL ASSESSMENTS

##### 9.1.4.1 BARTHEL INDEX

The Barthel Index of Activities of Daily Living (ADLs) is a rating scale for the measurement of activity limitations in patients with neuromuscular and musculoskeletal conditions in an inpatient and

outpatient rehabilitation setting. It has been used with rehabilitation patients to predict length of stay and to indicate the amount of nursing care needed.

The BI consists of 10 items that measure a person's daily functioning to assess functional independence in the domains of personal care and mobility. The items include feeding, transfers from bed to wheelchair and to and from a toilet, grooming, walking on a level surface, going up and down stairs, dressing, continence of bowels and bladder. The Barthel Index (BI) ranges from 0 (most disability) to 100 (no disability).

The BI assessment will be performed at Day 7 +/- 1 day (Visit 3) and Day 90 +/- 3 days (Visit 5), to determine an early post-acute phase performance status and at the end of the observation period (Day 90 +/- 3 days, EOS).

BI Assessment Form (Polish version) is provided in Appendix in [Section 14.1.3](#).

---

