#### 11.5.1.2 BASELINE DESCRIPTIVE STATISTICS

Age, sex, NIHSS, mRS, and Barthel index will be presented for Visit 0 overall and for each treatment arm and treatment group (study treatment and placebo).

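### Barthel, MoCA and HADS are analysed as change from a Day 7 score taken after treatment, which removes part, and possibly most, of the Day 90 effect; the Visit 0 Barthel listed for the baseline table is never collected

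*Protocol*

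**What the plan says.** Section 3.3, repeated in Section 1.1.3.3, defines the exploratory Barthel endpoint as "Change in Barthel Index score measured at Day 90 compared to Day 7" and the HADS endpoint as "Change on HADS scale measured at Day 90 compared to Day 7". MoCA is worded in the same way.

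Section 11.5.2.3 sets the analysis:

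- Barthel: the change score, for which the sentence names both Visit 3 and Visit 5, "will be assessed using ANCOVA with baseline Barthel Index score and treatment as independent variables". The result is to be given as an LS mean difference and 95% confidence interval.
- MoCA: "change from baseline (Day 7) to Day 90 will be analysed in the same way as Barthel Index".
- HADS: "assessment of mental condition collected on Day 7 and Day 90 will be analysed in the same way as Barthel Index".
- BNP uses the same method, but its baseline is the screening visit.

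The section also plans descriptive tables and boxplots of total scores by treatment.

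On timing, the Schedule of Activities (Section 1.3) puts treatment on Day 1 and counts Day 7 from the start of rtPA or its placebo. It marks Barthel, MoCA and HADS at Visits 3 and 5 only. Section 9.1.4.1 agrees for Barthel: "The BI assessment will be performed at Day 7 +/- 1 day (Visit 3) and Day 90 +/- 3 days (Visit 5". The Visit 0 list in Section 6.5.1 contains pre-stroke mRS and NIHSS, but no Barthel. Section 11.5.1.2 nevertheless states: "Age, sex, NIHSS, mRS, and Barthel index will be presented for Visit 0".

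**The concern.** The objectives in Section 3.3 ask how function, cognition and mood after the therapy compare with placebo. A Day 7 score already carries whatever the therapy did in the first week. Using it as both the reference for change and the covariate asks a different question: how the groups differ at Day 90 beyond the difference already seen at Day 7.

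The protocol treats Day 7 as an outcome time elsewhere. NIHSS change to Day 7 is a secondary efficacy endpoint, and Day 7 is the outcome time for BNP. The treatment is given once, and Section 6.4.1 ties its benefit to how soon after onset it starts. Early separation between the groups is therefore plausible, and that is the part of the effect this model takes out. The only planned model-based estimate for these three scales would then understate a lasting early benefit or a lasting early harm.

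The Visit 0 Barthel is a separate inconsistency. The baseline table calls for a value that no visit produces.

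**Working it through.** **Which baseline can the model use?**

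| Reading of the Barthel sentence | Support | Can it be run? |
|---|---|---|
| Change from Day 7 to Day 90 | Endpoint in Sections 1.1.3.3 and 3.3; explicit for MoCA in 11.5.2.3 | Yes, but the baseline is post-treatment |
| Change from Visit 0 to Day 7 and to Day 90 | Visit 0 Barthel in 11.5.1.2 | No; no Visit 0 Barthel in 1.3, 6.5.1 or 9.1.4.1 |

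The sentence is defective on either reading. For MoCA and HADS, Day 7 is the only earlier score.

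**What the model estimates.** Let d7 and d90 be the true treatment differences at Day 7 and Day 90, and b the common within-group slope of Day 90 on Day 7.

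- Outcome: Day 90 minus Day 7, with treatment difference d90 − d7.
- Slope of that change on Day 7: b − 1.
- Treatment coefficient: (d90 − d7) − (b − 1)·d7 = d90 − b·d7.

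ANCOVA on the Day 90 score with the same covariate gives the same coefficient. The share of d90 kept is 1 − b·(d7/d90), and the share lost is b·(d7/d90). A simulation of 200,000 patients with b = 0.7 and d7 = d90 = 0.5 SD returned 0.153, against 0.5 × (1 − 0.7) = 0.150 from the formula.

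**Size.** The protocol states neither b nor d7/d90, so both are assumptions. Share of the Day 90 effect kept:

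| d7/d90 | b = 0.3 | b = 0.5 | b = 0.7 | b = 0.8 |
|---|---|---|---|---|
| 0.5 | 85% | 75% | 65% | 60% |
| 0.75 | 77.5% | 62.5% | 47.5% | 40% |
| 1.0 | 70% | 50% | 30% | 20% |
| 1.25 | 62.5% | 37.5% | 12.5% | 0% |

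More than half is lost only when b·(d7/d90) > 0.5. A comparison of Day 90 scores, unadjusted or adjusted only for pre-treatment values, targets 100% of d90 in every row.

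**Illustration in power terms.** The protocol gives no effect size, SD or power for these scales. Its only sample size is 46 per group for the primary test (Section 11.3), and that figure reproduces. The fixed-design number is 39.8. One interim look raises it by a factor of 1.006 to 40.05, rounded up to 41. Then 41/0.9 = 45.6, rounded up to 46. This point does not affect it.

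Take 41 evaluable per group, an assumed Day 90 effect of 0.5 SD, two-sided 0.05, and residual SD √(1 − b²) for the Day 7-adjusted model. An unadjusted Day 90 comparison has 62% power. The planned model has:

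| | b = 0.5 | b = 0.7 | b = 0.8 |
|---|---|---|---|
| d7 = d90 | 26% | 16% | 11% |
| d7 = half of d90 | 50% | 54% | 62% |

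In the last cell the smaller residual SD offsets the smaller estimate. Power is then the same, but the estimate is still 60% of d90.

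**The case against.** Several things can fairly be said for the plan:

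- **Exploratory endpoints.** No decision rule or sample size rests on them. Function is compared at Day 90 by the mRS primary endpoint without any Day 7 reference, and NIHSS change has a true Visit 0 value. This stands, and it limits the consequence.
- **Total scores are described by treatment.** The Day 90 levels will therefore be visible. This also stands. What is missing is a model-based Day 90 contrast; the planned LS mean difference and interval come from the Day 7-adjusted model.
- **The SAP may settle details.** Section 11.5.3.1 defers exploratory analyses to it. But the protocol already fixes both the endpoint and the model, so this is a stated rule and not an omission.

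A reader might infer that the model removes most of the effect, or that an effective therapy would show about none. The documents do not support either as a general statement. The first needs b·(d7/d90) > 0.5, and neither quantity is given. The second describes a plain change-score comparison with d7 = d90, whereas the protocol specifies ANCOVA.

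A reader might also infer that early deaths make a harmful therapy look favourable among survivors. That risk is not quantified, and it is not peculiar to the Day 7 reference: a Day 90 comparison also has to deal with patients who die or cannot be tested. Their handling can properly be set in the SAP.

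**Conclusion.** The point holds for the three exploratory scales. The planned ANCOVA conditions on a post-treatment Day 7 score, and its coefficient does not answer the stated objective whenever the groups already differ at Day 7. The loss is part, and possibly most, of the Day 90 effect: 50–80% if d7 = d90 and b = 0.5–0.8, and 25–40% over the same b if d7 is half of d90. These ranges rest on assumed values and on a linear model with a common slope. That an effect present at Day 7 and lasting to Day 90 in the same direction is reduced does not depend on the particular values, as long as b is positive.

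The Visit 0 Barthel in Section 11.5.1.2 contradicts the Schedule of Activities, the Visit 0 list and Section 9.1.4.1. The primary conclusion and the sample size are unaffected.

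**What to change.** In Section 11.5.2.3:

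- Make the model-based contrast for Barthel, MoCA and HADS a between-group comparison of Day 90 scores, adjusted only for pre-treatment values already collected, for example Visit 0 NIHSS, age and pre-stroke mRS.
- Report Day 7 scores and Day 7-to-90 change descriptively.
- Keep the BNP ANCOVA, which has a true pre-treatment baseline.

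In Section 11.5.1.2, remove Barthel from the Visit 0 table. Set the handling of deaths and untestable patients in the SAP.

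**Cost.** The same data are used and no assessment is added. However, change from Day 7 is the defined endpoint in Sections 1.1.3.3 and 3.3, so that wording must be amended to match. The Statement of Compliance and Section 12.1 require protocol amendments to be approved before they are implemented.

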#### 9.1.5 NATRIURETIC PEPTIDE

Brain natriuretic peptide (BNP), also known as B-type natriuretic peptide or ventricular natriuretic peptide is a hormone secreted by cardiomyocytes in the heart ventricles in response to stretching caused by increased ventricular blood volume. It is postulated that BNP can serve as a prognostic biomarker of AIS (Refs.)

B-type natriuretic peptide (BNP) and N-terminal pro-BNP (NT-proBNP) assist in the diagnosis of heart failure (HF). The difference between BNP and NT-proBNP is that one is biologically active as a hormone - BNP and NT-proBNP is biologically inactive. BNP has a much shorter half-life, thus

NT-proBNP, as a consequence of longer half-life, circulates in higher concentrations in the bloodstream.

The diagnostic sensitivity and specificity of BNP and NT-proBNP is comparable; both provide prognostic information in patients with heart failure, coronary artery disease, and valvular heart disease.

Change in BNP or NT-proBNP concentration from baseline (Visit 0) till Day 7 +/- 1 day (Visit 3) will be an exploratory endpoint, and the prognostic value of BNP or NT-proBNP concentration during AIS course and correlation with actual treatment will be evaluated.

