## 11.5 STATISTICAL ANALYSES

### 11.5.1 GENERAL ASSUMPTIONS

#### 11.5.1.1 STATISTICAL SIGNIFICANCE ASSUMPTIONS

Statistical significance level will be equal to 0.20 for purpose of primary endpoint analysis and 0.05 otherwise. P values  $\geq 0.001$  will be reported to 3 decimal places; p-values less than 0.001 will be reported as “<0.001”. The mean, standard deviation, and any other statistics other than quantiles, will be reported to one decimal place greater than the original data. Quantiles, such as median, or minimum and maximum will use the same number of decimal places as the original data. Estimated parameters, not on the same scale as raw observations (e.g. regression coefficients) will be reported to 3 significant figures.

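### The exploratory natriuretic-peptide endpoint accepts either BNP or NT-proBNP but is analysed as raw change in one ANCOVA; if both assays are used, the estimate belongs to neither analyte and loses precision (minor).

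*Protocol*

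**What the plan says.** Protocol Section 3.3 (and the matching synopsis table, 1.1.3.3) sets a single endpoint: "Change in BNP or NT-proBNP plasma concentration at Day 7 compared to pre-treatment levels". Section 9.1.5 repeats it: "Change in BNP or NT-proBNP concentration from baseline (Visit 0) till Day 7 +/- 1 day (Visit 3) will be an exploratory endpoint". The schedule in Section 1.3 and the visit lists in 6.5.1 and 6.5.4 show the test as BNP/NT-proBNP at Visits 0 and 3. None of them names one analyte or asks for the same one at both visits.

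Section 9.1.5 also states that the two differ in level: "NT-proBNP, as a consequence of longer half-life, circulates in higher concentrations in the bloodstream". It gives no ratio.

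Section 11.5.2.3 then says the "change between baseline (Screening visit) and Day 7 will be analysed in the same way as Barthel Index". The Barthel method is that change "will be assessed using ANCOVA with baseline Barthel Index score and treatment as independent variables", and "LS mean difference between placebo and active drug with 95% confidence interval will be provided". If equal variance or normality looks grossly violated, "other methods including an ANCOVA on ranks model or an appropriate transformation of endpoint might be considered". The model has no assay term, no split by assay and no default log scale.

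**The concern.** The Barthel Index is one scale from 0 to 100. This endpoint can be either of two quantities that the protocol itself places at different levels. A raw-change model treats a unit of one as equal to a unit of the other. With a mixed set of assays, the LS mean difference depends on how many patients had each test, and the patients on the higher-level analyte dominate both the estimate and its variance. At stake are the readability and precision of one exploratory result. The prognostic use of the peptide described in 9.1.5 also needs values that can be compared across patients.

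**Working it through.** **Inputs from the protocol.** 46 subjects per group, 92 per arm, 10% drop-out (11.3); significance level 0.05 outside the primary endpoint (11.5.1.1); model and effect measure from 11.5.2.3.

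**Assumed, because the protocol gives none of them.** Level ratio k of NT-proBNP to BNP, share s of patients on NT-proBNP, lognormal spread, and a 30% proportional reduction that is the same on both analytes. Each patient has the same analyte at both visits unless stated.

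**The plan's own figure.** No size is stated for this endpoint. The only sample-size figure is 46 per group for the primary endpoint, used here just to set n. Fixed design: 0.48 × (0.8416 + 0.5244)² / 0.15² = 39.8. A two-look Hwang-Shih-DeCani design (γ = −4 assumed, look at half the information) gives 40.05 and reproduces the stated interim level of 0.0238. Then 40.05 / 0.9 = 44.5, so 45 against 46 stated, which is close enough.

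**1. What the pooled difference estimates.** If the BNP difference in means is D, the same proportional effect on NT-proBNP is k·D, and the pooled expectation is D × [(1 − s) + s·k].

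With log-SD 0.8, in units of the BNP median, D = −0.30 × exp(0.8²/2) = −0.30 × 1.377 = −0.41. An all-NT-proBNP trial at k = 6 would give 6 × −0.413 = −2.48. For mixtures at k = 6:

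| Share on NT-proBNP | Multiplier | Formula | Simulated ANCOVA (82 per arm) |
|---|---|---|---|
| 20% | 2.0 | −0.83 | −0.79 |
| 50% | 3.5 | −1.45 | −1.38 |
| 80% | 5.0 | −2.07 | −2.00 |

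One and the same 30% reduction is reported as three different numbers. None is the BNP effect or the NT-proBNP effect.

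**2. Power, separating pooling from the raw scale.** 46 per group, 50:50 mix, log-SD 1.0 at baseline and 0.5 for change, two-sided 0.05:

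| Analysis | Power |
|---|---|
| Raw ANCOVA, one analyte | about 60% |
| Raw ANCOVA, pooled, k = 3 / 5 / 10 | about 53 / 47 / 42% |
| Log-ratio ANCOVA | about 92% |

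Pooling costs about 60 − 53 = 7, 60 − 47 = 13 and 60 − 42 = 18 points. The other 92 − 60 = 32 points come from analysing skewed data on the raw scale. With 1,500 replicates the simulation error is about √(0.6 × 0.4 / 1500) = 1.3 points.

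Hand check of the log model: |ln 0.7| = 0.357; SE = 0.5 × √(2/46) = 0.104; 0.357/0.104 = 3.42; Φ(3.42 − 1.96) = 0.93.

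**3. Different spreads.** With 82 per arm, log-SD 0.8, visit correlation 0.8 and shares of 20%, 50% and 80%, raw power is 0.74–0.76 with one analyte. Pooled, it is 0.65–0.70 at k = 3, 0.51–0.68 at k = 6 and 0.38–0.66 at k = 10. Rank ANCOVA gives 0.75–0.82, and log-ratio ANCOVA with an assay term 0.90–0.91. The direction is the same in every mixed scenario.

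**4. Validity.** With no treatment effect (k = 6, 50% mix), the pooled raw ANCOVA rejects 4.7% of the time, which is nominal.

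**5. Does the log scale need an analyte term?** With the same analyte at both visits, log(kF/kB) = log(F/B), so the scale factor cancels in the outcome. Log-ratio ANCOVA without the term also has about 92% power and recovers a ratio of 0.70. The term only tidies the baseline covariate.

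**The case against.** The strongest reply has four parts.

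- **Exploratory and partly for the SAP.** Section 11.5.3.1 leaves exploratory analyses to a SAP, which is not shown, and an assay covariate or eCRF field could sit there or in data-management documents. That stands for the detail. It does not cover the choice of model, which 11.5.2.3 states together with its covariates and effect measure.
- **The fallback.** A reader might infer that the permitted transformation cannot help without an analyte term. That is not so: step 5 shows that a log transformation largely repairs the same-analyte case. What remains is that the fallback is optional and tied to gross violation, and that its other named route, ranks, recovers only part of the power and gives no effect in concentration units.
- **Validity.** A reader might infer that the comparison is invalid or cannot address its objective. Randomisation protects the test, and type I error is nominal. Only the size of the effect is hard to read.
- **Switching between visits.** A reader might infer that patients will have BNP at one visit and NT-proBNP at the other. Nothing forbids it, but Visits 0 to 3 are expected within one hospital stay, change most naturally means change in one analyte, and no switch rate is given. It is a possibility to close off, not a predicted loss. If 10% did switch (an arbitrary rate), log ANCOVA with an analyte term would fall to 80%, 67% and 52% power at ratios of 3, 5 and 10. Excluding those patients restores about 88–89%, so an analyte term alone would not be enough.

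**Conclusion.** The point holds as a minor one. The protocol defines one endpoint on either of two analytes, says their levels differ, and prescribes a raw-change ANCOVA that ignores which was measured. If both are used, the LS mean difference is a mix-weighted figure that belongs to neither analyte, and precision falls. If all sites use one analyte, pooling does no harm, but the protocol does not require that.

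It would be tempting to set 53%, 47% and 42% against 92% and call the whole gap the cost of pooling. The one-analyte figure of about 60% shows otherwise: pooling accounts for roughly 7 to 18 points and the raw scale for about 32. The direction follows from the text and simple algebra. The sizes rest on assumed level ratios, mix, spread and effect.

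**What to change.** In 11.5.2.3, take this endpoint out of the Barthel method. Make the default an ANCOVA of log(Day 7 / Visit 0) on log baseline and treatment, with analyte as a covariate. Report a geometric mean ratio with its 95% CI, and show results by analyte as well.

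In 6.5.1, 6.5.4 and the schedule in 1.3, require the Visit 3 test to use the same analyte as Visit 0, and record analyte and unit in the eCRF if it does not already hold them. Exclude patients with mismatched analytes from this analysis.

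The cost is a few sentences and at most one or two eCRF fields, with no extra sampling. The downside is that a few patients with mismatched tests may be lost from an exploratory analysis.
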